## Abstract

Non-specific low back pain represents 90–95% of all cases of low back pain and it has a prevalence of 18% in the adult population, assuming a great socioeconomic impact. The main objective of this observational case-control study study is to evaluate if there are differences in the simultaneous contraction of the core muscles between nonspecific low back pain and healthy subjects. This study will be carried out in the Physiotherapy department of the University of Alcalá. Eighty-two participants <18 years old, will be recruited, paired with NSLBP (n = 41) and healthy (n = 41). The main outcome will be the onset muscle contraction of lateral abdominal wall (internal oblique, external oblique and transversus abdominis), pelvic floor, lumbar multifidus and respiratory diafragm. The maneuvers that the subjects will perform will be abdominal drawing in maneouver, contralateral arm lift, valsalva, and voluntary pelvic floor contraction in sitting and standing. As a secondary objective, to analyze the amount of contraction of each muscle group and the capacity of the diaphragms to be excreted in both groups of subjects. Finally, to relate pain and disability.

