### Sample size calculation

The sample size calculation has been carried out with the program ‘GPower 3.1.5’ and based on the main inter-subject factor of a mixed 4-by-2 analysis of variance (ANOVA). An effect size of 0.25 was estimated, with a correlation between repeated measurements of 0.50, a power of 80% and a level of 0.05. The resulting sample size was 82 subjects.

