### Outcomes

The primary outcome will be the onset muscular contraction of the four core muscle groups during the Abdominal Drawing in Maneouver (ADIM), Contralateral Arm Lift (CAL), Valsalva maneuver, and voluntary contraction of the PF, in sitting and standing positions:

Onset muscular contraction of the three muscles that conform the Lateral Abdominal Wall (LAW); Transversus abdominis (TrA), Internal oblique (IO), External oblique (EO).Onset muscular contraction of Lumbar Multifidus (LM).Onset excursion of the Diaphragm (DPH).Onset excursion of the Pelvic Floor (PF).

The secondary outcomes are; the percentage of change in muscle thickness in the LM and LAW (IO,EO,TrA) represented as average contraction thickness (cm)–average thickness at rest (cm) / average thickness at rest (cm)*100 [12]; the excursion of the DPH [15] and the excursion of the bladder trough the contraction of the PF muscles [16]. Finally, the degree of disability through the Oswestry disability questionnaire) [17].

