### Data processing

The data will be collected from December 2021 to February 2023. Written informed consent will be obtained from all participants prior to recruitment. The participant Data Collection form that contains information as socio-demographic data (height, weight, and personal medical history) will be completed by the participant and a 10-question questionnaire (S4 Appendix) designed by the research team that will allow the participant to be assigned to the case or control group. The Visual Analog Scale (VAS) [14] as well as the Oswestry Dissability Index scale [17] will be completed only by subjects who have been assigned to the case group. To ensure the authenticity of the data, all individuals will complete the questionnaires independently.

Once the participant has completed all the forms, the customized fixation belt will be placed on the subject, with its corresponding US probes. With the US M-Mode, the start of movement of each specific muscle group will be identified. These results will be compared with the morphological characteristics of each muscle group such as the % of change in thickness of the LM and the LAW, and the endopelvic and respiratory diaphragms excursions.

The US videos and images of each probe will be displayed in four tablets through the USG Wireless program. These tablets are connected to a computer through a customized video capture card.

To objectify the onset muscle contraction of each muscle group, the OBS (Open Broadcaster Software® V.28.1.2 Boston, MA 02110–1301 USA) will be used. The OBS will allow to observe the four videos all at once, where the specific and global muscle contraction can be visualized in a simpler and clearer way. In addition, a stopwatch will be used in the same program to visualize the onset muscle contraction.

The collected data will be saved and imported to a personal laptop for later measurement by a blinded examiner using the program Free software FIJI® V.2.9.0 Cambridge CB3 0HA, UK [28].

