For the analysis of the differences between the groups in the continuous quantitative dependent variables that meet the assumption of normality, a mixed 4-by-2-by-2 covariance analysis (ANCOVA) will be used, with the maneuver (ADIM, CAL, Valsalva, voluntary PF contraction) and the position (sitting, standing) as intra-subject factors, the group (pain, healthy) as an inter-subject factor, and the BMI (Body Mass Index) as a covariant. The association between abdominal muscle thicknesses with gender, age, and BMI was examined using Pearson’s correlation coefficient and multiple regression analysis. Compliance with the assumption of sphericity will be assessed with the Mauchly test and that of equality of covariance matrices with the Box test. The partial eta-square coefficient (p2) will be used as an estimator of the size of the ANCOVA main effects and interactions.

It will be performed the Kruskal-Wallis H test for analyze the differences between independent variables (cases and controls) and the onset muscular contraction, as a qualitative ordinal dependent variable. On the other hand, the t-Student test for independent samples with Bonferroni correction will be used for the analysis of post-hoc pairwise comparisons. Cohen’s d (d = 2t / √g) will be used as estimator of the effect size of the post hoc comparisons [31].

If any continuous quantitative dependent variable does not meet the assumptions for carrying out the ANCOVAs, robust analogous methods will be used that do not require compliance with those assumptions, following the procedures described by Wilcox [31]

All analyses will be carried out with the software R Version 4.1.0 (R Core Team (2021). R: A language and environment for statistical computing. R Foundation for Statistical Computing, Vienna, Austria. URL https://www.R-project.org/). An α level of 0.05 with 95% confidence intervals (CI) will be assumed for all analyses.

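### Onset, the primary outcome, is assigned a two-group Kruskal-Wallis test that ignores the eight repeated conditions, does not match the model behind N = 82, and uses no defined measure of timing between muscles

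*Protocol article*

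**What the plan says.** All references are to the protocol article.

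- **Objective (Abstract).** The study is to "evaluate if there are differences in the simultaneous contraction of the core muscles between nonspecific low back pain and healthy subjects". The end of the Introduction words the main objective as synergies between the core muscle groups.
- **Primary outcome (Outcomes).** "The primary outcome will be the onset muscular contraction of the four core muscle groups", in four maneuvers and two positions. The list names six structures: three abdominal wall muscles, lumbar multifidus, diaphragm and pelvic floor.
- **Measurement (Data processing).** Onset is identified in M-mode with the four videos viewed together, and "a stopwatch will be used in the same program to visualize the onset muscle contraction".
- **Reliability (Statistical analysis).** Onset is to be assessed with the ICC, SEM, minimum detectable difference and Bland-Altman limits.
- **Group comparison (Statistical analysis).** "It will be performed the Kruskal-Wallis H test for analyze the differences between independent variables (cases and controls) and the onset muscular contraction", with onset taken "as a qualitative ordinal dependent variable". The mixed 4-by-2-by-2 ANCOVA, with maneuver and position within subject and BMI as covariate, is worded for continuous variables only, and so is the robust fallback. Bonferroni is mentioned only for post-hoc t tests.
- **Sample size.** 82 subjects, from the between-subject factor of a mixed 4-by-2 ANOVA with effect size 0.25, correlation 0.50, power 80% and level 0.05.

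**The concern.** The primary outcome receives the only main group comparison that leaves out the repeated structure and the covariate. The continuous secondary outcomes receive the full model. Three statements do not fit together: onset is continuous for reliability, ordinal for the group comparison, and sized as the outcome of a mixed ANOVA.

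Kruskal-Wallis assumes independent observations, and the article does not say how eight conditions and six structures enter it. Pooling the conditions would invalidate the primary p-value. Testing them separately would give many underpowered tests with no stated error control. Neither is the analysis that 82 subjects were calculated for.

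In addition, the objective is about how muscles act together, but no lag, spread or synchrony category is defined, and neither is the coding of the ordinal variable.

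**Working it through.** **Inputs from the article.** Two groups of 41 (Abstract); effect size 0.25, read as Cohen's f as G*Power does for ANOVA, hence d = 2f = 0.5 for two equal groups; correlation ρ = 0.50; α = 0.05; power 80%; 4 × 2 = 8 conditions; six structures. **Assumed:** ρ of 0.3 and 0.7 as a range around 0.50; equal correlation between all conditions; normal data in the simulations.

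**1. Reproducing N = 82.** For the between-subject factor, the noncentrality is λ = f²·N·m / [1 + (m − 1)ρ], with 1 and N − 2 degrees of freedom. With m = 4:

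- N = 80: λ = 0.0625 × 80 × 4 / 2.5 = 8.0, power 0.798.
- N = 82: λ = 0.0625 × 82 × 4 / 2.5 = 8.2, power 0.808.

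So 82 is the smallest even N that reaches 80%. The figure is right for a repeated-measures ANOVA with four measurements.

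**2. Kruskal-Wallis on the eight conditions pooled.** Treating 8 × 82 = 656 values as independent understates the variance of the group contrast by the design effect 1 + 7ρ. At ρ = 0.50 this is 4.5, so the test statistic is inflated by √4.5 = 2.12. The approximate true size is 2[1 − Φ(1.96 / 2.12)] ≈ 0.36. Simulation (41 per group, no group difference) gives:

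| ρ | Type I error, 4,000 runs | Type I error, separate 3,000 runs |
|---|---|---|
| 0 | 0.050 | – |
| 0.3 | 0.270 | 0.259 |
| 0.5 | 0.348 | 0.342 |
| 0.7 | 0.428 | 0.422 |

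**3. Kruskal-Wallis in each condition separately.** Each test keeps its 5% size.

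- *Power in one condition.* With m = 1, λ = 0.0625 × 82 = 5.125. Power is 0.61 for a t test and about 0.59 for a rank test (asymptotic efficiency 0.955).
- *Bonferroni over 8* (α = 0.05 / 8 = 0.00625): 0.30 and 0.28.
- *N for 80% power in a single condition:* 128.
- *At least one false positive over 8 uncorrected tests, one muscle:* 1 − 0.95⁸ = 0.34 if independent; simulated 0.30, 0.25 and 0.20 at ρ = 0.3, 0.5 and 0.7.
- *Number of tests* if all structures are examined: 6 × 8 = 48.

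**4. A model using all eight conditions.** With m = 8, λ = 0.0625 × 82 × 8 / 4.5 = 9.11. Power for the group effect at N = 82 is 0.847, and 74 subjects would give 80%. The planned sample is therefore adequate for such a model under the article's own inputs.

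**5. Objective against variable.** The objective concerns "differences in the simultaneous contraction of the core muscles between nonspecific low back pain and healthy subjects". The outcome is listed muscle by muscle, and the test compares groups on an ordinal onset value whose coding is not given. If that value is the firing order, it carries some information on coordination but drops the delay between muscles. If it were a synchrony grade it would address the objective, but the article does not say so.

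**The case against.** The strongest defence is that the article never says the conditions are pooled. Run per muscle and condition, each Kruskal-Wallis test is valid, and a condensed article may leave such detail to a fuller plan. A valid test could also be run on one summary value per participant: simulating the test on each subject's mean gave a size of 0.046 at ρ = 0.50. This stands in part. The 35% figure applies to pooling only and should not be read as the error rate of the plan. But no per-participant summary is defined, and the assigned test and the scope of the ANCOVA are stated rules, not omissions. Separate testing does not deliver the planned 80% power either.

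The 0.50 correlation was given for the ANOVA, not for ordinal onset scores. That also stands, and is why a range is shown.

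A reader might infer that the plan cannot measure simultaneity and that the main objective goes unanswered. The documents do not support this. The ordinal coding is undefined, an ordinal synchrony category would address simultaneity directly, and firing order is relevant to synergy. Nor do they define simultaneity as the gap between first and last onset.

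A reader might also infer that precise onset times are already in hand. The article says that the stopwatch helps to visualize onset, with four wireless probes shown on four tablets and joined by a capture card. It gives no time resolution or synchronisation between devices. Because it gives no onset times either, any power comparison in milliseconds would rest on invented values.

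**Conclusion.** The point holds in this form: the stated test for the primary outcome does not account for the eight repeated conditions, has no maneuver, position or BMI term, conflicts with the continuous treatment of onset in the reliability analysis, and is not the analysis that N = 82 was derived for. The consequence depends on a choice the article does not make:

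- **Pooled:** type I error about 35% at ρ = 0.50, about 26–43% over 0.3–0.7.
- **Separate:** valid tests with power of about 0.6 each (about 0.3 with Bonferroni over eight) against the planned 0.80, and about a 25% chance of a false positive per muscle if uncorrected.

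These figures assume f = 0.25 (d = 0.5) in each condition, equal correlations and approximately normal data. On the objective, the supported conclusion is the limited one: no defined variable compares timing between muscles, so simultaneous contraction is at best answered indirectly.

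**What to change.** In the Statistical analysis section:

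1. Define a between-muscle timing variable for each maneuver and position. Lag or spread of onset times is one option, if the time resolution and synchronisation of the recordings allow it. Otherwise use an ordinal synchrony category with its coding written out. A spread from first to last onset depends on two extreme readings, so its reliability should be checked before it is adopted.
2. Replace Kruskal-Wallis for onset with one repeated-measures model containing group, maneuver, position, BMI and a participant random effect. Use a linear mixed model (or a robust version) if onset is kept as a time, and a cumulative-link mixed model if it is kept ordinal. Use the same scale in the reliability analysis.
3. Name the group main effect on the between-muscle variable as the single primary test, with muscle-specific onsets as supporting analyses.
4. State in the Sample size calculation that N = 82 applies to this model. With eight conditions and the article's inputs, power is about 0.85 for a continuous outcome. If the outcome stays ordinal, recheck the figure for that model.

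The cost is some extra R code, a rewritten paragraph and a check of timing precision. No additional participants are needed under the article's own assumptions. Whether the existing recordings suffice for a lag or spread depends on that check.

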**Fig 1 pone.0285441.g001:**
[figure not shown]
Customized fixation belt.

Three of the probes corresponding to the LAW, LM and DPH will be positioned on the right side of the patient as the sound amplifying window offered by the liver is needed to measure the excursion of the DPH [15]. The fourth probe corresponding to the PF is placed transversely and suprapubically on the subject [16]. The probes placement will correspond to the measurement areas of each muscle group that have been previously validated by different authors [15, 16, 19, 20]. The four US images will be visualized and unified in a computer through a video capture card, where the onset muscle contraction and the morphology of the muscles will be analyzed.

An US analysis will be carried out to evaluate the onset muscle contraction of the four core muscle groups in a global and synergic manner, as well as their individual morphological characteristics during the ADIM, CAL, voluntary PF contraction and Valsalva maneuvers in sitting and standing. The measurements will be taken in these two positions since they have been assumed in as possible risk factors for the appearance of NSLBP and its maintenance [21].

The maneuvers and the positions will be randomized by means of opaque envelopes that will be assigned to each patient to eliminate possible biases. All tests will be performed once in sitting and standing positions. with a 2 minutes break between maneuvers. The authors of this study considered that 2 minutes break between each maneuver and 2 minutes of rest between positions, being low intensity tests, could be enough to avoid participant fatigue. All the maneuvers will be taught before each measurement.

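### Post-hoc tests are planned as plain independent-samples t-tests, so group contrasts lose the BMI adjustment and any maneuver or position contrast would ignore the pairing

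*Protocol article*

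**What the plan says.** The Statistical analysis section of the protocol article sets out the model for continuous outcomes: "a mixed 4-by-2-by-2 covariance analysis (ANCOVA) will be used". Its repeated factors are "the maneuver (ADIM, CAL, Valsalva, voluntary PF contraction) and the position (sitting, standing) as intra-subject factors". The remaining terms are "the group (pain, healthy) as an inter-subject factor, and the BMI (Body Mass Index) as a covariant".

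For the follow-up step one test is named: "the t-Student test for independent samples with Bonferroni correction will be used for the analysis of post-hoc pairwise comparisons". The sentence does not limit these comparisons to one factor, mentions neither a paired test nor a model-based contrast, and does not carry BMI forward. Cohen's d, computed as twice t over the square root of a symbol printed as g, is the effect size for these comparisons.

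Three other statements bear on this:

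- Procedures: "All tests will be performed once in sitting and standing positions". Every participant therefore contributes to every maneuver and position.
- Sample size calculation: the plan works "with a correlation between repeated measurements of 0.50".
- Statistical analysis, on the purpose of the ANCOVA: "For the analysis of the differences between the groups in the continuous quantitative dependent variables".

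**The concern.** The follow-up test does not match the model it follows, and the consequence depends on which pairs are compared.

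**Group contrasts.** Cases and controls are different people, so an independent-samples test suits the design. It has no covariate, however. The protocol itself gives reasons to expect BMI to matter: the Introduction lists obesity among the risk factors for non-specific low back pain, Participants describes convenience sampling, and Statistical analysis plans to examine abdominal muscle thickness against BMI. Contrasts within a maneuver and position, which readers will interpret most closely, would be unadjusted while the overall test is adjusted. The two could disagree for no reason other than BMI.

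**Maneuver or position contrasts.** These compare measurements on the same participants. An independent-samples test treats them as unrelated, overstates the standard error and loses power.

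**Working it through.** **Inputs from the protocol.** N = 82 (41 per group), f = 0.25, correlation between repeated measurements ρ = 0.50, α = 0.05, power 80%, 4 maneuvers, 2 positions.

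**Assumed, not in the protocol.** BMI–outcome correlation r = 0.2 to 0.5; BMI difference between groups Δ = 0 to 0.5 SD; within-subject difference δ = 0.3 SD (range 0.2 to 0.5); alternative ρ of 0.3 to 0.9.

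**1. The plan's own figure.** For the between-subject factor with m = 4 repeated measurements:

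λ = f²·N·m / (1 + (m − 1)ρ) = 0.0625 × 82 × 4 / 2.5 = 8.2, with 1 and 80 degrees of freedom.

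Power is 0.808, and 82 is the smallest even N that reaches 80%. The stated sample size reproduces and is not in question.

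**2. Group contrast without BMI (41 per group).** With no BMI-adjusted group effect, the unadjusted difference has bias r·Δ in outcome SDs. The t statistic has noncentrality r·Δ·√(41/2). Simulation with 20,000 runs per row, two-sided at 5%:

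| r | Δ (SD) | Bias (SD) | Rejection rate |
|---|---|---|---|
| 0.2 to 0.5 | 0 | 0 | 4.9% to 5.1% |
| 0.2 | 0.25 | 0.05 | 5.5% |
| 0.2 | 0.50 | 0.10 | 7.0% |
| 0.3 | 0.25 | 0.075 | 6.1% |
| 0.3 | 0.50 | 0.15 | 10.3% |
| 0.5 | 0.25 | 0.125 | 8.7% |
| 0.5 | 0.50 | 0.25 | 20.1% |

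Check of the last row: noncentrality 0.25 × √20.5 = 1.13 against a critical t of 1.99 (80 df) gives 20.1% from the noncentral t.

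These rates are per comparison, before Bonferroni. If the family were the 4 × 2 = 8 maneuver-position cells (an assumption), the threshold would be 0.05/8 = 0.00625 with critical t 2.81. The last row would then reject in 5.2% of cases instead of 0.6%. Bonferroni lowers the rate but leaves the bias unchanged.

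For scale, f = 0.25 with two equal groups corresponds to d = 2f = 0.5. A bias of 0.05 to 0.25 SD is thus 10% to 50% of the planning effect.

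**3. Within-subject contrast by an independent-samples test (n = 82).**

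- Variance of the mean difference assumed by the test: 2σ²/n.
- Actual variance: 2σ²(1 − ρ)/n.
- Ratio of standard errors: 1/√(1 − ρ) = 1/√0.5 = 1.41.
- Type I error: P(|Z| > 1.96 × 1.414) = 0.0056; simulation (40,000 runs) gives 0.0058. The paired test gives 0.049.

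Power from the same simulation at δ = 0.3 SD, ρ = 0.50:

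| Threshold | Independent t | Paired t |
|---|---|---|
| 0.05 | 0.48 | 0.77 |
| 0.05/6 (all six maneuver pairs) | 0.15 | 0.51 |

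The analytic approximation, 1 − Φ((t_crit − δ√(n/2))/√(1 − ρ)) for the independent test and the noncentral t for the paired test, gives 0.47 and 0.77 at 0.05.

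Range over δ at ρ = 0.50, threshold 0.05, same formulas: 0.16 versus 0.43 at 0.2 SD, and 0.96 versus 0.99 at 0.5 SD.

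Range over ρ at δ = 0.3 SD, threshold 0.05: with ρ = 0.3, type I error is 0.018 and power 0.47 versus 0.62; with ρ = 0.9, type I error is essentially 0 and power 0.43 versus 1.00.

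**The case against.** The best defence is that only pain-versus-healthy comparisons are meant. The ANCOVA is introduced for differences between the groups, the main objective is a group difference, and no stated objective compares one maneuver with another or sitting with standing. Following up an interaction by comparing the groups in each maneuver-position cell gives several comparisons and explains the Bonferroni correction. The independent-samples test and the between-group d formula both fit this. A reader might infer that maneuver pairs must be included because maneuver is the only factor with more than two levels. The text does not support that. It also does not exclude such pairs: the sentence is unrestricted, and effect sizes are planned for all main effects and interactions. The figures in step 3 of the working are therefore conditional.

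It can also be said that the overall group test keeps BMI, that demographic homogeneity is to be tested, and that BMI imbalance may turn out small. All of this is true, and with no imbalance the rejection rate stays near 5%. But a homogeneity test does not adjust a contrast, and the post-hoc step as written has no covariate. The Abstract calls the participants paired, but no matching variable is named, so balance in BMI cannot be presumed.

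On the effect size, a reader might take g for the number of groups and conclude that d would be grossly inflated. Nothing supports that reading. Other symbols in the section are damaged or untranslated, and g is most plausibly a truncated symbol for degrees of freedom. What remains is that 2t/√df is a between-group formula.

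**Conclusion.** The point holds on either reading, with different consequences.

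- **Pain versus healthy (the natural reading):** the test form is suitable, but the BMI adjustment is lost. Bias is 0.05 to 0.25 SD and rejection 5.5% to 20% at nominal 5% under the assumed correlations and imbalances, with no material effect if BMI is balanced. The protocol gives neither the correlation nor the imbalance, so this is a range and not a forecast.
- **Maneuver or position (not excluded):** the test is wrong for correlated data. At the plan's ρ of 0.50 the standard error is 1.41 times too large, type I error is about 0.6%, and power for an assumed 0.3 SD falls from about 0.77 to 0.47. The error is conservative: it hides differences and does not create false positives.

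The reach is limited mainly to the continuous secondary outcomes (thickness change and excursions). A reader might infer that the primary analysis is compromised, but onset is assigned to the Kruskal-Wallis test as an ordinal variable, and the overall ANCOVA group test remains BMI-adjusted. The change should be made, but the design does not depend on it.

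**What to change.** Replace the t-tests with contrasts of estimated marginal means from the fitted model, adjusted by Bonferroni or Holm:

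- group contrasts within a maneuver and position: BMI-adjusted;
- any maneuver or position contrast: within-subject error.

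State which of these comparisons are planned, so that the size of the multiplicity family is known. Use d = 2t/√df, with df defined, only for between-group contrasts.

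The cost is a change of wording. No further data or participants are needed, and such contrasts are standard in R, the software already named.

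### For the continuous secondary outcomes, a failed Mauchly or Box test appears to move a variable out of the BMI-adjusted ANCOVA, although neither check has much bearing on the case-control effect

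*Protocol article*

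**What the plan says.** All of the following is in the Protocol article.

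- **Model (Statistical analysis).** For "continuous quantitative dependent variables that meet the assumption of normality, a mixed 4-by-2-by-2 covariance analysis (ANCOVA) will be used", with maneuver and position as within-subject factors, group as the between-subject factor, and "the BMI (Body Mass Index) as a covariant".
- **Checks (same section).** "Compliance with the assumption of sphericity will be assessed with the Mauchly test and that of equality of covariance matrices with the Box test".
- **Response to failure (same section).** "If any continuous quantitative dependent variable does not meet the assumptions for carrying out the ANCOVAs, robust analogous methods will be used". The sentence goes on to cite reference 31 for the procedures. No epsilon correction or other intermediate step is mentioned. No particular robust procedure is named for this design, and the text does not say whether BMI stays in.
- **Reach of the rule.** The Outcomes section makes onset of contraction primary. The Statistical analysis section treats onset as ordinal and gives it a Kruskal-Wallis test. The rule therefore covers the continuous secondary outcomes compared between groups: percentage thickness change of LM, TrA, IO and EO, and the diaphragm and pelvic floor excursions. By the Data processing section, the disability index is completed by cases only.
- **Size.** The Sample size calculation section bases 82 subjects on the between-subject factor of a 4-by-2 mixed ANOVA. The Abstract splits them 41 and 41.

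**The concern.** The usual answer to failed sphericity is to adjust the degrees of freedom of the within-subject tests, or to fit a model that does not assume sphericity. The covariate-adjusted group comparison is left alone. Here the only stated answer is to leave the model, and the decision is taken variable by variable from the data.

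The case-control contrast for one muscle could then be a BMI-adjusted difference in means, and for the next a robust contrast of unspecified form, because of a check that says little about that contrast. The comparison is not randomised and uses convenience sampling (Participants section), and BMI is the only covariate in the group model. Whether it survives the switch matters. The four maneuvers are different tasks, so equal variances and correlations across them cannot be taken for granted.

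**Working it through.** **1. The plan's own figure.** Inputs from the Sample size calculation section: "An effect size of 0.25 was estimated, with a correlation between repeated measurements of 0.50", "a power of 80% and a level of 0.05". Taking 0.25 as Cohen's f (the letter is not given) and m = 4 repeated measures:

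λ = f²·N·m / [1 + (m − 1)ρ] = 0.0625 × 82 × 4 / 2.5 = 8.2, with 1 and 80 df, gives power 0.808.

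The stated 82 is reproduced. The effect that was sized is the group main effect.

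**2. What the group test depends on.** With complete data, and BMI constant within a subject, the group test is a regression of each subject's mean over the 8 cells on group and BMI. Only the variance of that mean, 1ᵀΣ1/64, enters. Sphericity is a condition on contrasts between cells, so it plays no part.

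If the groups differ in variance, then with n = 41 each and no covariate the pooled squared standard error is [(s₁² + s₂²)/2] × (2/41) = s₁²/41 + s₂²/41. This is the same as the unequal-variance form. With BMI in the model the equality is only approximate, so it was simulated.

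**3. How often the checks reject.** Position has two levels and raises no sphericity question. That leaves three tests: Mauchly for maneuver, Mauchly for maneuver by position, and Box on the 8 × 8 matrices. If they were independent at 0.05, the chance of at least one false rejection is 1 − 0.95³ = 0.143.

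Simulation: 41 per group, 8 cells, correlation 0.5 unless stated, 800 to 1,500 studies per scenario. The SDs and the alternative correlations are assumptions, because the documents give none.

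| Assumed structure | At least one check rejects | Type I error, BMI-adjusted group test |
|---|---|---|
| All assumptions hold | 14–15% | 6.1% |
| Maneuver SDs 1, 1, 1.1, 1.2 | 33–35% | 5.3% |
| One maneuver SD 1.25× | 52–54% | 5.2% |
| Maneuver SDs 1, 1, 1.25, 1.5 (epsilon 0.90) | 92% | not run |
| One maneuver SD 1.5× | 98% | 5.5% |
| One maneuver SD 1.5×, and case SD 1.5× control | 99.9% | 4.7% |
| Correlations 0.4 to 0.7 | 98% | 4–6% (BMI not confirmed in this run) |

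With 1,500 studies the simulation error around 5% is 1.96 × √(0.05 × 0.95/1500) = 1.1 points, so none of the type I errors stands out from 5%. Skewed scenarios are left out, since a skewed variable would mostly leave through the separate normality condition.

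**4. Different methods across outcomes.** Take a switch probability of 0.14 per outcome (all assumptions true) and treat the six outcomes as independent. The chance that some switch and some do not is 1 − 0.86⁶ − 0.14⁶ = 0.60. Dependence between outcomes would change this, and the documents give nothing to estimate it.

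**5. If BMI were dropped on switching (an assumption).** With a 20% trimmed test without BMI, simulated power falls by about 9 to 12 points. Type I error rises to about 11% when BMI differs by 0.5 SD between groups and is related to the outcome.

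A hand check, assuming a correlation of 0.3 between BMI and the subject mean: shift 0.5 × 0.3 = 0.15 SD; standard error √(2/41) = 0.221 SD; ratio 0.68. Then P(Z > 1.28) + P(Z < −2.64) = 0.100 + 0.004, about 10%.

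**The case against.** Several points on the other side have force.

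- **The link is read in.** The fallback sentence names neither Mauchly nor Box, and a fuller plan might add an epsilon step. That is possible. But those two tests are the named checks of ANCOVA assumptions, and the only stated response to unmet assumptions is the switch. The plain reading stands.
- **The primary outcome is untouched.** This stands. Because the sample size rests on the group effect, a reader might infer that the main case-control test is at risk. As the analysis is written, it is not.
- **The fallback is not unnamed.** This stands too: a class of methods and a source are cited. What is open is the procedure for a 4-by-2-by-2 design with a covariate.
- **BMI may be kept.** A method described as analogous to an ANCOVA may well retain the covariate. A reader might infer that the adjustment would probably be lost for most outcomes. The documents do not say so, and step 5 applies only if it is dropped.
- **The rates depend on unknown variances.** This is correct. A reader might infer that the ANCOVA would seldom be run. With only a correlation of 0.50 and no SDs in the protocol, that cannot be derived, and the assumed cases run from about 15% to nearly 100%.
- **No harm from switching itself is shown.** This is partly fair. The simulation shows that the displaced test was sound. It does not show that the full two-stage procedure inflates error. Muscle is also not a factor in the model, so no formal comparison between muscles is spoiled; the loss is in reading six results side by side.

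**Conclusion.** The point holds for the six continuous secondary outcomes, as a weakness of the decision rule and not as an error in the primary analysis. Mauchly and Box say little about the group effect, since sphericity does not enter it and the groups are equal at 41. Yet a failure of either appears to replace the BMI-adjusted model.

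Under the assumed structures at least one check rejects in about 15% of studies when everything holds. It does so in about 50% to 98% when one maneuver's SD is 1.25 to 1.5 times the others. The adjusted group test stays at 4% to 6%. The consequence is that outcomes could be tested by different methods and may lose the BMI adjustment.

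This rests on the plain reading of the fallback sentence, complete data, each check at 0.05, and the assumed covariance structures. It is a change worth making because it is cheap.

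**What to change.** Replace the switch rule in the Statistical analysis section for the continuous secondary outcomes:

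- Keep the BMI-adjusted model for every one of them.
- Test within-subject terms with the Greenhouse-Geisser correction, or fit a linear mixed model with unstructured covariance.
- Do not use Mauchly or Box to choose the analysis.
- Name the robust procedure, retain BMI in it where possible, and report it as a sensitivity analysis for all six outcomes, whatever the checks show.

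A log transform should not be part of the remedy. Thickness is analysed as percentage change from rest, which can be zero or negative.

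The cost is a few lines of text, a little more analysis, and slightly larger p-values for the within-subject terms. No new data are needed and the sample size does not change.
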